### 2.2. Secondary Objectives

Improvement of the study participants’:Self-management.Level of independence in the activities of daily living (ADL).Quality of life.Adherence to home-based rehabilitation and pharmacological and non-pharmacological treatment.Need for caregivers (family, care providers…).Recurrent stroke and the complications related to stroke.A number of hospital readmissions, emergency care, and outpatient visits to the hospital and primary care centers.

Also, the study will evaluate:Cost-effectiveness of the developed system.Accessibility of the developed system.Sustainability of the developed system.User’s satisfaction (by users, we mean stroke survivors, caregivers, and professionals using the developed system).Possible adverse events that the system can cause on the study participants.

In addition, the efforts will be made to identify new variables related to the prognosis of stroke.

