### 2.14. Statistical Analysis

Each variable will be characterized using frequency distributions central tendency, such as the mean and median, and to determine variability standard deviation or the interquartile range according to its distributional characteristics.

Comparisons between groups and intra-groups will be performed using parametric tests provided that the distributional characteristics of the data meet the requirements; otherwise, non-parametric tests will be used.

Comparisons between two continuous variables will be performed using the Pearson or Spearman correlation, depending on the distributional characteristics.

The comparison of proportions between categorical variables will be carried out by means of a chi-squared test or its corresponding Fisher correction. The continuous variables will be compared using the comparison of the means (t-student test or ANOVA) if the sample distribution is normal, and if the distribution is not normal, then the non-parametric Mann-Whitney U test will be utilized.

The populations will be analyzed by intention to treat analysis and as stated in the protocol.

A micro-data collection form will be developed. The analysis of costs will be done from the perspective of the health system and direct costs. The data collected will serve to estimate the actual cost of procedure data under usual practice conditions and costs derived from the implementation of the new intervention in the different contexts under study.

The collection of these data, together with data on effectiveness and utility, will enable subsequent studies on economic analysis and cost-effectiveness/utility to help decision-making on which alternatives are most effective and efficient from the point of view of the health system.

The SPSS 23.0 program for Windows (SPSS Inc, Chicago, IL, USA) will be used. A p-value of 5% or lower is considered to be statistically significant. The statistical analysis will be blind to the intervention group.

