	Pharmacological			x	x
Complications	Stroke recurrences Number of readmissions Number of consultations to the emergency department Number of visits/telephone calls to a general doctor Number of visits to specialist Number of secondary complications due to stroke			x	x

**Table 2 mps-02-00050-t002:** Schedule of the trial variables for caregivers.

Caregivers	Variables/Scales	Event Visit	Baseline Visit	First Visit	Final Visit
Health Literacy	Test of Functional Health Literacy in Adults Stroke Patient Education Retention	x	x		x
Quality of Life	SF-36	x	x		x
Burn-Out	Caregiver Strain Index		x		x
Self-Management	Family needs of stroke patient questionnaire		x	x	x
Satisfaction Questionnaire	Satisfaction Questionnaire		x		x
Usability	System Usability Scale			x	x

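### Under section 2.14's single normality rule, skewed visit counts, and by default any cost comparison, go to a rank test that does not compare mean cost or visit rate

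*Protocol article*

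**What the plan says.** Section 2.14 gives a general rule: "Comparisons between groups and intra-groups will be performed using parametric tests provided that the distributional characteristics of the data meet the requirements", with non-parametric tests otherwise. It then names a t-test or ANOVA for continuous variables that look normal. For the rest its instruction is: "if the distribution is not normal, then the non-parametric Mann-Whitney U test will be utilized". Proportions go to chi-squared or Fisher. No count model and no mean-based method for skewed data is mentioned. The section opens by saying that each variable will be described by mean and median with a measure of spread.

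Costs have a separate paragraph: "The analysis of costs will be done from the perspective of the health system and direct costs". Its stated purpose is estimation ("The data collected will serve to estimate the actual cost of procedure data under usual practice conditions"), and the data, together with effectiveness and utility data, "will enable subsequent studies on economic analysis and cost-effectiveness/utility". Section 2.2 nevertheless lists cost-effectiveness among the things this study will evaluate.

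The counts are a secondary objective in section 2.2: "A number of hospital readmissions, emergency care, and outpatient visits to the hospital and primary care centers". Section 2.10 makes health-care resource use a secondary outcome. Table 1 schedules the counts at the first and final visits, for example "Number of consultations to the emergency department".

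**The concern.** The rule chooses the test from the shape of the data, not from the question. For a health system the question about costs is the difference in arithmetic means, because mean cost times number of patients is the budget. For visits it is the rate per patient over follow-up. The Mann-Whitney U test asks whether a patient from one arm tends to rank above a patient from the other, which is a different quantity.

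For costs the two can disagree in sign because of how STARR works. Every intervention patient receives devices, training and technical support (sections 2.4 and 2.9), so most of that arm moves up in rank. The hoped-for saving is fewer readmissions (section 3), which concern a minority of patients but carry most of the money. The trial could then report STARR as significantly more expensive when its mean cost is equal or lower. Even when the directions agree, the reported test gives no estimate of cost saved or visits avoided with its uncertainty, which the later economic studies will need.

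**Working it through.** **1. Which rule applies.** The sentence that names Mann-Whitney speaks of continuous variables, so counts reach it through the general between-group rule. Costs are assigned no test. If arms are compared on cost at all, the general rule is the only one available.

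**2. What each method targets.** Mann-Whitney: θ = P(X > Y) + ½P(X = Y), null value ½. Health-system cost question: Δ = mean cost STARR − mean cost control. Visit question: the ratio of visits per unit of follow-up time. Nothing ties the sign of θ − ½ to the sign of Δ when the arms differ in shape.

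**3. Inputs.** The article gives no costs, admission risks or visit rates, so there is no figure of the plan to reproduce and all values below are assumptions. Arm sizes come from the article: 72 / 2 = 36 (section 2.13) and 40 / 2 = 20 (section 2.4). The level is two-sided 5%. The article does not say how normality is judged; Shapiro-Wilk was assumed.

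**4. Costs, first set of assumptions.** Background cost is gamma, mean 600, SD 400. Admission cost is log-normal, mean 6000, log SD 1. Admitted: 20% control, 12% STARR. STARR adds a fixed cost c per patient.

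Control mean = 600 + 0.20 × 6000 = 1800. STARR mean = c + 600 + 0.12 × 6000 = c + 1320.

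| c | STARR mean | True saving | Mann-Whitney: STARR significantly dearer (36 per arm) |
|---|---|---|---|
| 0 | 1320 | 480 | under 1% |
| 100 | 1420 | 380 | about 5% |
| 200 | 1520 | 280 | about 21% |
| 300 | 1620 | 180 | 47–49% |
| 400 | 1720 | 80 | 70–72% |

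With equal true means (c = 300, 15% admitted: 300 + 600 + 0.15 × 6000 = 1800), Mann-Whitney declares STARR dearer in 51–53% of trials. Welch's t-test does so in at most 3% in every row. With 20 per arm the wrong-direction share runs from about 4% (c = 100) to somewhat under half (c = 400). The ranges reflect repeated simulation runs.

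**5. Costs, second set of assumptions.** STARR: 600 + gamma (mean 2 × 250 = 500) + 5% admitted at mean 6000, so mean 600 + 500 + 300 = 1400. Control: 200 + 500 + 0.20 × 6000 = 1900. Simulated medians are 1040 and 729, and P(STARR > control) = 0.67. Mann-Whitney is significant for STARR dearer in 46% (20 per arm) and 69% (36 per arm) of trials, and for STARR cheaper in 0%.

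**6. Counts.** Negative binomial, assumed means and dispersion parameter k.

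- Equal dispersion (k = 0.8, means 2 and 3): ranks agree with the means. Wrong-direction significance is at most 0.4%. Mann-Whitney finds the right direction in 13% and 20% of trials (20 and 36 per arm), Welch in 13% and 24%.
- Very unequal dispersion (k = 5 and 0.4), means 2 and 2.5: wrong-direction significance 16% (20 per arm) and 25% (36 per arm). With equal means of 2, Mann-Whitney rejects in about 28% and 44%.

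**7. How often the rule would choose the rank test.** Shapiro-Wilk rejects normality in 100% of trials for the first cost set and in 79–100% of samples for the second (18 to 36 per arm). It rejects in 96–100% for low overdispersed counts (mean 2, k = 0.8), but in only 11–15% for Poisson counts with mean 10.

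**The case against.** **Costs are not sent to Mann-Whitney.** A reader might infer that the plan commits to testing costs by ranks. It does not: the cost paragraph is about estimation, names no test and leaves economic evaluation to later studies. This stands. What remains is that section 2.2 has this study evaluate cost-effectiveness, and the only between-group rule offered for such data is the normality rule.

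**Not always non-normal.** A reader might also infer that all such data must go to Mann-Whitney. Frequent contacts, such as general-practice visits, can look close to normal (step 7). Usually, for rare or overdispersed events, is as far as one can go.

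**Arm means will be reported.** They will, under the descriptive paragraph, so a raw difference can be worked out. What the stated rule lacks is that difference as the analysis result, with an interval. A condensed article may leave intervals to a fuller document, but here the article fixes a test, and a fuller plan that follows it inherits the wrong target.

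**Counts rarely reverse.** This is correct. No per-patient addition operates on counts, and with equal dispersion the direction is right. For counts the objection removes the wrong-direction argument but not the estimand argument.

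**The cost figures are invented.** They are assumptions, and the result moves from under 1% to about 70% as one of them changes. They show that reversal is possible under STARR's cost structure, not how likely it is in this trial.

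**Pilot, secondary outcomes.** True, and it limits the weight of the point. Section 3 itself concedes that six months may be short for significant results on recurrence, complications and deaths, which makes estimates with intervals more useful than a rank p-value.

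**Conclusion.** The point holds in this limited form. Section 2.14 offers one between-group rule for numeric data, and it would usually take rare, skewed visit counts to Mann-Whitney, along with any between-arm cost comparison by default. For both, that is the wrong estimand and leaves no between-arm effect estimate with an interval. For costs there is also a risk of a significant result in the wrong direction: about 5% to 70% of trials at 36 per arm for an assumed STARR cost of 100 to 400 per patient, and under 1% if STARR adds no cost. For counts, wrong direction arises only if dispersion differs clearly between arms, and the documents give no reason to assume that. All magnitudes rest on assumed costs and rates. The primary outcome is untouched.

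**What to change.** In section 2.14, exempt costs and counts from the normality rule:

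- **Costs:** difference in arithmetic mean cost between arms with a bootstrap 95% confidence interval.
- **Counts of readmissions, emergency visits and consultations:** rate ratio with 95% confidence interval from a log-link count model with log follow-up time as offset. Use the negative binomial, or Poisson with robust variance if events are too few for it to converge.
- **Medians and rank tests:** description only.

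The fallback is needed. Under the first set of assumptions only about 36 × 0.20 + 36 × 0.12 = 7.2 + 4.3 = 11.5 admissions are expected (0.16 per patient), and at that rate a default negative binomial fit failed or gave no p-value in 12–23% of 500 simulated trials per setting.

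The cost is two or three sentences and minor programming, with no new data or visits. With so few events the intervals will be wide, which is a fair account of what a trial of this size can say.

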### 2.15. Quality Control and Assurance

For ensuring the quality of the study, data will be collected on the adherence to the intervention, the inclusion, and follow-up of all patients, as well as monitoring and quality of data entry.

If there were to be suspicion of a serious violation of the trial protocol, it would imply a significant effect on:(a)the physical or psychological integrity or safety of patients during the trial, or(b)the values of the study. The study sponsor will be contacted as soon as possible. In any case, all violations will be notified to the relevant authorities in accordance with current legislation.

The protocol will not be modified without the consent of the principal investigator and the sponsor. Any modification of the protocol requires Ethics Committee approval prior to its implementation except to avoid immediate risks in patients.

The study documents will be reviewed, comparing them to the originals. The researcher will be informed of the progress of the study, and the suitability of the facilities will be evaluated on an ongoing basis.

In addition, the study may be evaluated by internal auditors of the sponsor and inspectors designated by health authorities who will be allowed access to the database, original documents, and other study files. Audit reports by the sponsor will be kept confidential.

The current legislation will comply with the terms of protecting the confidentiality of data (Regulation UE 2016/679). For this, each patient will receive an alphanumeric identification code in the study that will not include any data that allows their personal identification. The principal investigator will have an independent list that will allow the connection of the identification codes of the patients participating in the study with the clinical and personal data. This list will never leave the center. Only the researchers responsible for the study and listed in the clinical protocol approved by the Ethics Committee, as well as the competent authorities, will have access to the study data.

The trial sponsor and the researchers of the study declare his or her willingness to make the results of the trial public, preferably through scientific means of dissemination, that is, publications submitted to the peer review process.

### 2.16. Limitations of the Study

One of the variables that will be measured is usability. It must be borne in mind that part of the patients who survived a stroke do not only have disabilities but, in some cases, there are older patients who are not used to the use of new technology and this could be a problem to adapting to the STARR system. For this, applications for tablets and smartphones are very easy to use, intuitive, and guide the patient without great technological knowledge. In addition, all the wearables used in the study will be Bluetooth, facilitating the transmission of data in this way.

Another limitation could be the use for end users within the health sector since the STARR system would allow patients to be monitored, as well as to perform clinical controls and changes in their medical guidelines. But it could lead to failure if the system overloads professionals’ workload and is not easy to be managed. This fact will be taken into account when implanting alarms and communication systems with the health system so that it is manageable by the professionals and really helps to control and improve the patient.

## 3. Discussion

Quality of life can be improved by self-management interventions that accomplish more than a single domain of change. The success of these interventions depends on participation levels, impairment of participant, health services’ use, health behavior, costs, participant’s satisfaction, and associated adverse events during the intervention period. However, these interventions are often difficult, time-consuming, and human resources intensive [24].

In order to ease this intervention, new technologies could help. Furthermore, there is a rapid growth worldwide in mobile phone use, internet connectivity, and digital health technology.

A Cochrane review about mobile phone messaging for facilitating self-management in long-term conditions, such as diabetes, hypertension, and asthma, was published in 2012. They found moderate evidence in the improvement of health outcome and self-management for the three conditions, but only low evidence in health service utilization in asthmatic patients [15].

In our study, we took into consideration all the aspects of stroke and its self-management. In 2016, Spassova et al. have published an RCT, a computerized phone-based lifestyle coaching prevention system, with a 6-month follow-up in 94 patients at high risk of stroke. They reported a statistical improvement in blood-pressure measures, LDL, triglyceride values, and nutritional quality (fruit, vegetable, fewer sweets). They combined remote surveillance with tailored advice by phone call, and they concluded that it is usable and effective without being able to register severe events, such as stroke or deaths [19].

In July 2017, Lui S et al. concluded in their review of the literature that mobile health is a viable strategy to enhance stroke risk factor control, improving the glycemic control and smoking abstinence at 6 months [21].

Not only the chronic patients could benefit from this intervention but also the acute and subacute ones, as Vanacker et al. showed in their article of March 2017 where a well-trained nurse controlled remotely the stroke knowledge, secondary prevention, and rehabilitation treatment [20].

According to our study protocol, we will study chronic and disabled patients who live at home. We will try to improve all the aspects of self-management due to a holistic intervention, so if effective, the results of this study will enable stroke patients and their caregivers to deal better with the everyday life obstacles of stroke, however, there is no study about the caregivers and health professionals’ point of view of the new technology-based medicine in the reviewed literature.

The intervention is expected to promote a lifestyle change, not only promoting the therapeutic physical activity, but also alcohol and smoking consumption diminution, healthy diet implementation, and improving health literacy and information management among survivors, caregivers, and health professionals.

Adherence to the treatment, both pharmacological and non-pharmacological, is expected to increase. Control of modifiable cardiovascular risk factors is envisaged to get better. In consequence, it might reduce the recurrence of secondary strokes, reduce the number of complications, reduce the number of consultations, and readmissions, all in all, it might reduce the overload and hence reduce the health systems costs.

Caregivers are also expected to obtain assistance and related care information from health system professionals during the study. It is well known that assessing the needs of family caregivers is important for health care workers in understanding problems from the caregivers’ perspectives [24]. By improving the self-management of stroke survivors, it is intended not only to empower caregivers but also to improve their quality of life.

A follow-up of 6 months may be a short time to establish statistically significant results about the stroke recurrence, detected medical problems, complications (falls, fractures, depression, pain, etc.), and deaths. However, the intention of the research team is to perform the first analysis with the results of the 6 months of intervention and, if these are positive, then to conduct a trial with 3–5 years of follow-up.

One of the limitations of the study could be a lack of adherence to the designed application since it is a population, in some cases with advanced age and with physical limitations, resulting from their disease. The usability analysis will be determinant to develop a long-term study. In any case, studies carried out in similar populations make us think that usability will not be a problem for the continuity of the study and to demonstrate the improvement of self-management and quality of life of stroke survivors and caregivers. The potential effectiveness of the STARR system lies in the active participation of patients and caregivers.

Taking into consideration that the number of stroke survivors is increasing all around the world, a large number of stroke survivors, caregivers, and also health systems could profit from this intervention.

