### 2.12. Follow-up Period

All patients recruited for the research clinical trial (RCT) will be reassessed during external consultations at month 3 ± 1 week (1^st^ visit) and at month 6 ± 1 week (final visit).

All the participants will get the same reassessment at the event day (evaluation a), recruitment visit (evaluation b), 3 months later (evaluation c), and 6 months of follow-up (evaluation d) taking into consideration that not all the tools are administered at each time.

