### 2.13. Sample Size

To obtain a power of 80% to detect statistically significant differences when comparing the null hypothesis—a bilateral chi-squared test for two independent samples—taking into account that the level of significance is 5% and assuming that the proportion of dependence in the control group is 41.5% [23] and the proportion in the intervention group is 15%, a total of 72 stroke survivors will be needed. Taking into account the expected percentage of dropouts of 10%, it will be necessary to recruit 80 patients. The dependence will be measured by SSSMQ and Family needs of stroke patient questionnaire.

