## Figures and Tables

**Figure 1 mps-02-00050-f001:**
[figure not shown]
Diagram of the study.

**Table 1 mps-02-00050-t001:** Schedule of the trial variables for patients.

Stroke Survivors	Variables/Scales	Event Visit (a) Month 0	Baseline Visit (b) Month 6	First Visit (c) Month 9	Final Visit (d) Month 12
Inclusion	Age	x	x		
	Stroke characteristics and type	x	x		
	Modified Barthel Index	x	x		x
	Modified Rankin Scale	x	x		x
	Mississippi Aphasia Screening Test [MAST]	x	x		x
	Montreal Cognitive Assessment [MoCA]	x	x		x
	Gijon’s social-familial evaluation scale	x	x		
	Comorbidities	x	x		
	Charlson Comorbidity Index	x	x		
Socio Demographic	Gender, ethnic group, deprivation index, hand dominance, education level, type of job, hobbies	x	x		
Clinical/ Neurological	Cardiovascular risk factors	x	x	x	x
	Neurological physical examination: Medical Research Council Scale [MRC]	x	x	x	x
	Mississippi Aphasia Screening Test [MAST]	x	x		x
	Montreal Cognitive Assessment [MoCA]	x	x		x
	Functional Ambulation Categories [FAC]	x	x	x	x
	10 m walking test/6 min walking test	x	x	x	x
	Berg Balance Scale [BBS]	x	x	x	x
	Frenchay Arm Test [FAT]	x	x	x	x
	Asworth Modified Scale for Spasticity	x	x	x	x
	Fatigue Severity Scale [FSS],	x	x	x	x
	Line Bisection Test	x	x	x	x
	Disphagia Sensitivity Campimetry	x	x	x	x
	Pain Analogic visual scale for pain Analgesic treatment consumption	x	x	x	x
	Depression and Anxiety: Golberg Scale	x	x	x	x
	Stress	x	x	x	x
	Weight, Height, BMI, waist size, waist-to-hip ratio	x	x	x	x
	Blood pressure, heart rate, glycemia	x	x	x	x
	Need of upper limb orthoses, lower limb orthoses, and canes and wheelchair use in outdoor activities	x	x	x	x
Health Literacy	Test of Functional Health Literacy in Adults Stroke Patient Education Retention	x	x		x
Usability	System Usability Scale			x	x
Life Style	Mediterranean Diet Assessment Tool Physical activity/Exercise Toxic consumption	x	x	x	x
Blood Test	Lipidic profile (total cholesterol, high-density lipoprotein (HDL), low-density lipoprotein (LDL), cholesterol), glycemia, proteins, albumin, HbA1c, Apoprotein B, and Apoprotein A1	x	x		x
Activities of Daily Living	Modified Barthel Index (BI) Lawton Index	x x	x x		x x
Quality of life	SF-36 Stroke Impact Scale (SIS)	x x	x x		x x
Self-Management	The Southampton Stroke Self-Management Questionnaire (SSSMQ)		x	x	x
	Satisfaction Questionnaire		x		x
	Quebec User Evaluation of Satisfaction with Assistive Technology			x	x
Adherence	Post-stroke checklist		x		x
	Non-pharmacological				

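### Usability is meant to steer the long-term study, but it is first rated at month 9 and never at discontinuation, so participants who leave before then have no score

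*Protocol article*

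**What the plan says.** The Discussion (section 3) gives usability a deciding role: "The usability analysis will be determinant to develop a long-term study". Shortly before, it makes the longer trial depend on the 6-month results: "if these are positive, then to conduct a trial with 3–5 years of follow-up".

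The instrument is the "System Usability Scale". Table 1 ("Schedule of the trial variables for patients") marks it at month 9 and month 12, and Table 2 ("Schedule of the trial variables for caregivers") marks it at the same two visits. Neither row is limited to one arm. Section 2.12 says "All the participants will get the same reassessment at the event day" and at the later evaluations. Its only caveat is that not every tool is used at every time point.

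Sections 2.7 to 2.9 give STARR to the intervention group only. Section 2.5 lets patients and caregivers withdraw at any time. It also lets the team withdraw them for loss to follow-up, serious illness of the main caregiver, or any problem thought to justify ending treatment. No usability rating is tied to any of these events. Section 2.13 plans for "the expected percentage of dropouts of 10" percent.

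**The concern.** A usability rating is informative only if it covers the people who tried the system, including those for whom it did not work. Training takes one week to 10 days (section 2.9), but the first rating comes 3 months after baseline. Anyone who leaves in between contributes nothing.

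Early leavers may include people who found STARR hard to use. Section 2.16 foresees that some older patients may struggle to adapt to new technology, and the Discussion names poor adherence to the application as one of the study's limitations. Section 2.5 is headed as withdrawal from the trial, yet its last reason speaks of withdrawal from treatment. Ending STARR can therefore end follow-up too.

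At stake is a figure that is too favourable just where the article says it will guide the next study. Separately, controls are scheduled to rate a system they do not have, so any score collected from them would mean nothing.

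**Working it through.** The documents state no usability sample size, threshold or expected score, so there is no planned figure to reproduce. The check has three steps.

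**1. Who has a score under the schedule (intervention arm)**

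| Situation | Scale due? |
|---|---|
| Uses STARR to month 12 | Yes, months 9 and 12 |
| Stops STARR, stays in follow-up | Yes, months 9 and 12: section 2.12 reassesses all recruited patients, and section 2.5 does not list non-use as a reason for withdrawal |
| Leaves between months 9 and 12 | Month 9 only |
| Leaves before month 9 | No score |

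Only the last row has no score at all.

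**2. How many**

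Inputs: 1:1 allocation (section 2.6); 80 to be recruited and 10% dropout (section 2.13); 40 to be analysed (section 2.4). The two totals differ, so both are shown.

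- Patients with a STARR system to rate: 80/2 = 40, or 40/2 = 20. The other half are controls.
- If the 10% dropout applies equally to both arms and all falls before month 9: 40 × 0.90 = 36 scored and 4 missing, or 20 × 0.90 = 18 scored and 2 missing.

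The number of caregivers is not stated, so they are not counted here.

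**3. Effect on the mean**

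Let S be the mean in those scored, L the mean that the missing would have given, and q the share missing. The mean over all who tried the system is (1 − q)S + qL, so the overstatement is q(S − L). The value S = 75 and the range L = 40 to 60 are assumptions.

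| Share missing | L = 40 | L = 50 | L = 60 |
|---|---|---|---|
| 10% | 3.5 | 2.5 | 1.5 |
| 20% | 7.0 | 5.0 | 3.0 |
| 30% | 10.5 | 7.5 | 4.5 |

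For example, with 4 of 40 missing and L = 40: (36 × 75 + 4 × 40)/40 = 71.5, and 75 − 71.5 = 3.5.

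Only the 10% row uses the plan's rate, and it puts all dropout before month 9. If half of it came later, q would be 5% and the overstatement 0.05 × 15 = 0.75 to 0.05 × 35 = 1.75 points for a month-9 score. The 20% and 30% rows show sensitivity only; the documents do not support those rates.

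**The case against.** The strongest reply is that follow-up does not depend on using the app. A reader might infer that everyone who gives up STARR goes unscored, so that the mean describes only persistent users and is inflated by construction. The documents do not support this. Section 2.12 brings back all recruited patients, section 2.5 does not list non-use as a reason for withdrawal, and section 2.14 states an intention-to-treat analysis. The gap is confined to those who leave before month 9, and the mean is inflated only if they would have rated STARR lower.

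A reader might also count half the sample as lost data because controls cannot rate STARR. That goes too far as well. The natural population for the scale is the system's users, which is how section 2.2 describes users when it speaks of satisfaction. No between-arm comparison of the scale is announced, and a footnote limiting the rows could sit in the full protocol. Nor do the two statements about the longer trial contradict each other: good 6-month results and acceptable usability can both be required. Usability is missing from the lists in sections 2.2 and 2.10, but the title and section 2.16 name it, so listing it there would only be a clarification.

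Finally, section 2.15 already collects adherence to the intervention, and section 2.4 says STARR will try to find out why a user does not adhere.

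Most of this stands and limits the point. It does not close the gap. Neither intention to treat nor adherence data supplies a rating from someone who left before the first one was taken. On controls, section 2.12 does more than omit a detail: it states the same reassessment for all and qualifies it by time, not by arm.

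**Conclusion.** The point holds in a limited form. The measure that the article calls decisive has no rating from intervention-arm patients or caregivers who leave before month 9. Any resulting error is probably upward, but that is a judgement: it requires early leavers to rate STARR lower than those who stay.

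At the plan's own dropout rate, taken as equal in both arms and all before month 9, the overstatement is 1.5 to 3.5 points under the assumed means (75 in those scored, 40 to 60 in those missing). It is smaller if some of the dropout comes later. Scheduling the scale for controls is a lesser fault of labelling. Neither affects the primary outcome. The change is still worth making before enrolment, because a rating not taken at departure is hard to recover later.

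**What to change.** 1. In Tables 1 and 2, limit the usability rows to intervention-arm patients and their caregivers, and state that the scale is not compared between arms.
2. Besides months 9 and 12, ask for the scale when a patient or caregiver stops using STARR or leaves the trial, where they agree, and use that score in the usability analysis.
3. Report the result with the number who left early and the share still using the system at month 12, from the adherence data that section 2.15 already collects.

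Naming usability in section 2.10, and saying in the Discussion whether the longer trial needs the 6-month results, the usability result or both, would be useful but optional.

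The cost is some wording and one short form for a few participants. Some will not be reachable, so the gap will shrink rather than vanish. The usability figure may also turn out less favourable.
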